## Abstract

**Background:**

Evidence is emerging from school-based studies that physical activity might favorably affect children’s academic performance. However, there is a need for high-quality studies to support this. Therefore, the main objective of the Active Smarter Kids (ASK) study is to investigate the effect of daily physical activity on children’s academic performance. Because of the complexity of the relation between physical activity and academic performance it is important to identify mediating and moderating variables such as cognitive function, fitness, adiposity, motor skills and quality of life (QoL). Further, there are global concerns regarding the high prevalence of lifestyle-related non-communicable diseases (NCDs). The best *means to address this challenge could be through primary prevention.* Physical activity is known to play a key role in preventing a host of NCDs. Therefore, we investigated as a secondary objective the effect of the intervention on risk factors related to *NCDs. The purpose of this paper is to describe the design of the ASK study, the ASK intervention as well as the scope and details of the methods we adopted to evaluate the effect of the ASK intervention on 5*^*th*^*grade children.*

**Methods & design:**

The ASK study is a cluster randomized controlled trial that includes 1145 fifth graders (aged 10 years) from 57 schools (28 intervention schools; 29 control schools) in Sogn and Fjordane County, Norway. This represents 95.3 % of total possible recruitment. Children in all 57 participating schools took part in a curriculum-prescribed physical activity intervention (90 min/week of physical education (PE) and 45 min/week physical activity, in total; 135 min/week). In addition, children from intervention schools also participated in the ASK intervention model (165 min/week), i.e. a total of 300 min/week of physical activity/PE. The ASK study was implemented over 7 months, from November 2014 to June 2015. We assessed academic performance in reading, numeracy and English using Norwegian National tests delivered by The Norwegian Directorate for Education and Training. We assessed physical activity objectively at baseline, midpoint and at the end of the intervention. All other variables were measured at baseline and post-intervention. In addition, we used qualitative methodologies to obtain an in-depth understanding of children’s embodied experiences and pedagogical processes taking place during the intervention.

**Discussion:**

*If* successful, ASK could provide strong evidence of a relation between physical activity and academic performance that could potentially inform the process of learning in elementary schools. Schools might also be identified as effective settings for large scale public health initiatives for the prevention of NCDs.

**Trial registration:**

Clinicaltrials.gov ID nr: NCT02132494. Date of registration, 6^th^ of May, 2014.

## Background and objectives

The relation between physical activity and academic performance has received widespread attention owing to the increasing pressure on schools and teachers to provide children with a range of physical and intellectual capabilities. Physical activity might affect children’s academic performance [1] and cognitive function [2]. The school setting is the cornerstone of societies globally. Schools reach a diverse group of children from an early age, and provide a learning environment that can exert an influence on children across a long period of time. Therefore, schools provide potentially useful settings to implement strategies designed to increase children’s physical activity [3, 4].

Over the last decade, there has been a considerable increase in both the number and quality of school-based studies. However, as school based interventions are difficult to implement, many have not assessed academic performance or cognition with validated tests, others have lacked a theoretical framework or were not randomized, some were of short duration, delivered a small “dose” of physical activity, had a small sample size or involved promotion of physical activity by non-experts. Also, it should be noted that relatively few studies have measured physical activity objectively [1]. Hence, there is a need for high-quality studies that address these limitations.

Further, there are global concerns regarding the high prevalence of lifestyle-related non-communicable diseases (NCDs) [5]. The prevalence of *NCDs,* such as type 2 diabetes, is increasing worldwide, and they affect people of all ages, including children [6]. The ultimate costs are a decreasing quality of life and escalating healthcare expenditures [7]. *P*hysical activity is known to effectively prevent a host of NCDs [8], thus providing an important target for primary prevention.

Our primary objective is to investigate the effect of a one year school-based physical activity intervention (Active Smarter Kids; ASK) on academic performance on a sample of 10-year-old boys and girls attending elementary school in Norway. Due to the complex relation between physical activity and academic performance, we identified possible mediating and moderating variables (cognitive function, physical fitness, adiposity, motor skills and quality of life (QoL)).

Our secondary objective is to investigate the effect of ASK on modifiable lifestyle-related risk factors related to *NCDs, such as* physical activity and sedentary behavior, cardiorespiratory fitness, muscle strength, motor skills, adiposity, dyslipidemia and blood pressure.

## Methods/Design

### A. Study design, study population and inclusion criteria

The ASK study is a seven months cluster-randomized parallel group controlled trial, with random allocation at the school level with a 1:1 ratio. All children are in fifth-grade (10-year-olds) from the Sogn and Fjordane County, situated in the *western* part of Norway. Inclusion criteria were that schools should have at least seven children in fifth-grade; that children were healthy (with no serious or chronic illnesses) and able to participate in daily physical activity and physical education (PE). Participants had to be able to complete standard academic performance tests (our primary outcome).

Sixty schools, encompassing 1202 fifth-grade children, fulfilled the inclusion criteria, and agreed to participate. This represented 86.2 % of the population of 10-year-olds in the county, and 95.2 % of total possible recruitment. We randomized 30 schools for the intervention (I-schools) and 30 schools for the control (C-schools) arm. A neutral third party (Centre for Clinical Research, Haukeland University Hospital, Norway) performed the randomization. After randomization, three schools (two I-schools and one C-school) from the same municipality declined to participate. In total, 1145 (97.4 %) of 1175 children from 57 schools (28 I-schools and 29 C-schools) agreed to participate in the study.

### B. The ASK intervention (dose, intensity, teacher training and following up)

#### Dose

The ASK intervention consists of three components (in total 165 min/week). In order to optimize adherence, these were established as part of the mandatory school curriculum for all children attending I-schools:

**1)** ASK physically active educational lessons (3 × 30 min each week); Academic lessons in three core subjects, Norwegian, *mathematics* and English carried out in the school playground. **2)** ASK physical activity breaks during classroom lessons (5 min × 5 days each week). **3**) ASK physical activity homework prepared by the teachers (10 min daily; 5 × 10 min each week).

As a part of the mandatory school curriculum in Norway, children from both the I-schools and C-schools participated in curriculum-prescribed 90 min/week of PE and 45 min/week of physical activity, in total; 135 min/week. Therefore, the children from the I-schools performed 300 min/week of physical activity/PE, while the children from the C-schools performed 135 min/week of physical activity/PE. However, it was specified to the C-school that they could carry out the amount of physical activity/PE that they would have done regardless of the ASK study.

#### Intensity

The three physical activity components in the ASK intervention were planned so that activities were varied and enjoyable for the children. We emphasized to the ASK-teachers that all activities should include all children, especially those who were not particularly fit or enthusiastic about physical activity. Special attention was given to creating an encouraging and motivating atmosphere during lessons, in order to support positive feelings and attitudes towards physical activity. Approximately 25 % of daily physical activity in the ASK intervention was intended to be of vigorous intensity. This was defined as “children would be sweating and out of breath”. The vigorous activity component was achieved by selecting a variety of high intensity activities such as running, relay racing, obstacle courses and various forms of active play.

Fifty-nine ASK teachers led the physical activity component in the 28 I-schools. These ASK teachers are classroom teachers assigned by the school principal to teach 5th grade in the I-schools (independently of the ASK study). To ensure that teachers were empowered, supported and qualified to deliver the ASK physical activity intervention to their students, we conducted three comprehensive instructional seminars (April, June and September 2014) for the I-schools teachers. Further, we provided two regional refresher sessions during the intervention period (December 2014 and February 2015) to encourage teachers to share experiences and solve challenges together with each other and the research team. Finally, we provided teachers in I-schools with email- and telephone-support. We also provided a password protected ASK homepage (http://www.askstudy.no) that supplied teachers in I-schools with information, videos and physical activity lessons.

### C. Theoretical framework

The ASK study is embedded in a socio-ecological conceptual framework that focuses on positive physical activity behaviors [9]. In brief, the socio-ecological model acknowledges the role of proximal (e.g. individual and social) and more distal (e.g. school physical environment, school policy) determinants of health behavior change as necessary to achieve sustained positive health behaviors. To address individual and social determinants we adopted specific theoretical frameworks including Harter’s Competence Motivation Theory [10], Achievement goal theory [11] and Ryan & Deci’s self-determination theory [12]. In line with these theories the ASK intervention emphasizes creating autonomy supporting and mastery oriented teacher-student interaction in order to enhance students’ physical activity behavior by positively influencing their perception of competence, self-efficacy, and intrinsic motivation for physical activity.

### D. Outcome measures

All participating children were tested at baseline and post intervention. The exception was physical activity which was assessed at baseline, at the midpoint of the intervention period and at post intervention. We describe each variable assessed in the following sections.

### Academic performance (primary outcome)

Academic performance in **1)** reading, **2)** numeracy, and **3)** English was measured using specific standardized Norwegian National tests designed and administrated by The Norwegian Directorate for Education and Training (NDET) [13]. The three different tests were administered on three different days, both at the baseline and post intervention test. Tests are extensively verified for validity and reliability by NDET and are aligned with competencies demanded from all schools by the national curriculum. For ASK, we analyzed reading, numeracy and English individually and as a composite score.

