#### Power calculations/Sample size and power

The ASK study was designed to detect an effect size (Cohen’s D) of 0.35 between two groups for change in academic performance. Sample size calculations were performed using standard formulas, given ɑ = 0.05, 1-β = 90 %, group ratio 1:1 and correlation of repeated measurements = 0.7, leading to a naive n = 103 children in each group. Due to the cluster-randomized controlled trial (RCT) design, the sample size was corrected for the design effect using *formula 1;* Design Effect = 1 + [(CV^2^ + 1)*n – 1]* (ICC), where CV = coefficient of variation for n, n = number of children within each cluster, and ICC = intraclass correlation coefficient. Thus, after accounting for school clusters, we required a sample size of 468 children in each arm (INT; CON). This is based on an ICC = 0.15, n = 16.2 after accounting for 20 % attrition at the subject level, and CV = 0.72 (design effect correction factor = 4.54). The assumed ICC is a conservative estimate compared to the expected ICC of 0.03 to 0.07, which lay the foundation for the sample size of the A+ PAAC study [55]. For secondary outcomes we assume an ICC of 0.05 to 0.10 [56]. Accepting the assumptions above, the target sample size allowed us to detect a significant difference between the groups for variables reaching an effect size of 0.24 (ICC = 0.05) to 0.30 (ICC = 0.10) or higher.

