#### Plan for analysis

Our main analysis in order to assess the effectiveness of the ASK intervention are based on and intention to treat analysis [57, 58]. We also acknowledge the importance of conducting per-protocol analyses to determine efficacy based on schools that showed fidelity to the model and performed the physical activity intervention as intended [59]. Therefore, we conducted secondary analyses of children who participated in ≥80 % of the physical activity-based intervention and schools which delivered ≥80 % of the physical activity-based intervention as we deem this acceptable adherence to the intervention itself.

We describe missing data using appropriate flow charts [60] that also allowed for investigation of missing data mechanisms and assumptions that underpin statistical analyses. Missing data was imputed from all available relevant variables by means of multiple imputation using a Markov Chain Monte Carlo procedure with 20 iterations, with an assumption that data are missing at random. We performed sensitivity analyses to evaluate the stability of results under various assumptions of missing data.

We used a mixed-effects model to test the between-group difference (intervention vs. control) for the main outcome (academic performance), controlling for baseline values and including school as a random effect. The per-protocol analysis was adjusted for differences between groups as appropriate.

We conducted our analyses using the newest available version of IBM SPSS (IBM SPSS Statistics for Windows, Armonk, NY: IBM Corp., USA). A two-sided p-value ≤ 0.05 were considered statistically significant.

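### The article analyses the primary outcome four ways at one unadjusted 0.05 threshold and does not say which analysis decides; if any one sufficed, the false-positive chance would be about 10% to 13%

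*Protocol article*

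**What the plan says.** Three places in the protocol article bear on this.

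- **Section D, Academic performance (primary outcome).** Three national tests are taken, and the article then states: "For ASK, we analyzed reading, numeracy and English individually and as a composite score". That makes four analyses under the primary-outcome heading, with none ranked above the others.
- **Section F, Plan for analysis.** The mixed-effects model is described in the singular, "for the main outcome (academic performance), controlling for baseline values and including school as a random effect". The only criterion for significance is: "A two-sided p-value ≤ 0.05 were considered statistically significant". No testing order, adjustment or requirement of joint significance is given.
- **Section F, Power calculations/Sample size and power.** The trial was "designed to detect an effect size (Cohen’s D) of 0.35 between two groups for change in academic performance", with "1-β = 90 %, group ratio 1:1 and correlation of repeated measurements = 0.7" and alpha 0.05. This too is one comparison. The effect size, the correlation and the intraclass correlation (ICC) of 0.15 are not assigned to the composite or to any one subject.

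**The concern.** The sample-size and analysis sections treat academic performance as one variable, while the outcome section treats it as four. Read together, they leave four unranked routes to a claim on the primary outcome, each of which could be judged at 0.05. A result with one significant subject and a null composite could be presented as a positive trial. So could the reverse, and a reader would have no stated rule by which to object.

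This matters because the Discussion expects a positive result to inform curriculum and school policy as high-level evidence. A claim of that weight needs a known error rate, and a 5% rate attaches only to one test named in advance.

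**Working it through.** **1. The plan's own sample size.** Inputs from the power section: d = 0.35, two-sided alpha 0.05, power 90%, correlation of repeated measurements 0.7, ICC 0.15, cluster size 16.2, coefficient of variation 0.72.

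- Variance of change in SD units: 2 × (1 − 0.7) = 0.6.
- Naive n per group: 2 × 0.6 × (1.960 + 1.282)² / 0.35² = 102.9, so 103, as stated.
- Design effect: 1 + [(0.72² + 1) × 16.2 − 1] × 0.15 = 4.54, as stated.
- 103 × 4.54 = 467.6, so 468 per arm, as stated.

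The arithmetic is correct. It reproduces for a single test at 0.05 and so contains no allowance for several.

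**2. False-positive chance if any one of the four analyses sufficed.** The documents give no correlation between the subject tests, so it is assumed and shown as a range. Three standard-normal test statistics with common correlation r were simulated under no effect (4 million draws per value of r). The composite statistic is their sum divided by √(3 + 6r), which means equal weights. Each of the four is tested at |z| > 1.96.

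| r | At least one of four significant | Multiple of 5% |
|---|---|---|
| 0 | 16.1% | 3.2 |
| 0.5 | 13.0% | 2.6 |
| 0.6 | 12.1% | 2.4 |
| 0.7 | 11.1% | 2.2 |
| 0.8 | 9.9% | 2.0 |
| 0.9 | 8.4% | 1.7 |

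Four independent tests would give 1 − 0.95⁴ = 18.5%. That figure cannot apply here, because the composite is built from the other three.

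**3. The split result.** The composite alone is significant 5% of the time under no effect. The chance that at least one subject is significant while the composite is not is therefore 13.0 − 5 = 8.0% at r = 0.5, and 9.9 − 5 = 4.9% at r = 0.8.

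**4. What the remedies cost in power, at the planned size and inputs.**

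- One decisive test at 0.05: power 90.0%, 468 per arm unchanged.
- Bonferroni over three tests (0.0167 each): 80.2% per test.
- Bonferroni over four tests (0.0125 each): 77.2% per test. Restoring 90% needs a naive n of 140, and 140 × 4.54 gives about 636 per arm. That is 1,272 in all, more than the 1145 children who took part.

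**5. Error under a gatekeeping rule.** Suppose the composite is tested first and the subjects follow by Holm only if it is significant. If the composite has no true effect, any false claim first requires a false rejection there, which has a 5% chance. If the composite has a true effect, Holm holds the error across the three subjects at 5%.

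**The case against.** The strongest reply is that the article never makes four primary tests. It names one outcome and speaks of it in the singular in both the power and analysis sections. A fair reader could take the composite as the outcome and the subjects as its components. The 0.05 threshold is general and is not tied to each subject test. Neither 0.05 is offered as family-wise control over four tests. The article is also condensed, and an analysis plan that is not shown may name the decisive test or adjust for multiplicity.

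Much of this stands. A reader might infer that the trial's error rate on its primary outcome is twice the stated 5%, or that the trial has no control of error. The documents do not support either inference, because a rule that any one of four suffices is stated nowhere and a single decisive test of the composite would hold 5%. Nor can the size be fixed more narrowly than a range, since the correlations and the make-up of the composite are not given. A reader might also infer that the sample size is wrong; it is not.

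What does not fall away is the conflict inside the article. It does more than leave a detail to a later plan: it lists four analyses under the primary-outcome heading, gives one unadjusted threshold and sizes for one comparison. The singular wording elsewhere does not say that the composite is the one meant.

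**Conclusion.** The concern holds as a conditional one. The article does not identify which of its four analyses of academic performance decides the primary question. If significance on any one were taken as success, the false-positive chance would be about 10% to 13% for correlations of 0.8 to 0.5, about 8% at 0.9 and about 16% with no correlation. These figures rest on assumed, equal correlations, an equally weighted composite and an any-of-four reading that the article neither states nor excludes. The ambiguity itself rests on no assumption and should be removed, because it determines what counts as a positive trial.

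**What to change.** - Name one decisive confirmatory test. The composite at two-sided 0.05 is a natural choice; a fixed order among the four, or a rule that all three subjects must be significant, would also control the error.
- If the composite is chosen, test the three subjects only when it is significant, with Holm across them (0.0167, 0.025, 0.05). Otherwise report them as secondary estimates with confidence intervals.
- State which outcome the inputs d = 0.35, correlation 0.7 and ICC 0.15 describe. The 90% power carries over to the composite only if those inputs apply to it.
- The article describes its analyses largely in the past tense. If data have already been analysed or unblinded, disclose when the hierarchy was set, since one chosen after seeing results does not protect the error rate.

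The cost is a few sentences, with no further children or data. The price is interpretive: an effect in a single subject without an effect on the decisive test becomes a secondary result.

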### Cognitive function/Executive functions

We assessed the three core executive functions identified by Miyake et al. (2000) [14], i.e. inhibition, cognitive flexibility and working memory using four pen and paper tests. The tests were administered in a quiet room at the children’s school. All tests required 15–20 min to complete. **1)** To assess inhibition we used Golden’s version of the Stroop test [15, 16]. **2)** To assess cognitive flexibility we used two tests, one verbal (Verbal fluency) and one nonverbal test (The Trail Making Test) [17]. **3)** To assess working memory we used a digit span test with digits both forward and backward (Wechsler Intelligence Scale for Children, 4th ed; WISC-IV) [16].

### Physical activity and sedentary behavior

Physical activity was measured by triaxial accelerometry (ActiGraph GT3X+, LLC, Pensacola, Florida, USA). ActiGraph accelerometry uses the most widely applied instrument for objective assessment of physical activity and has been extensively tested for validity and reliability in children [18]. Children were instructed to wear the accelerometer on the right hip over seven consecutive days at all times, except during water activities or while sleeping. A wear-time of ≥ 480 min/day was applied as a criterion for a valid day. Periods of ≥ 20 min of zero counts are defined as non-wear time [19]. The number of ‘valid days’ vary depending on the analyses performed. Outcomes for physical activity levels are total physical activity level (counts/min), sedentary behavior (min/day and percentage of valid wear time), light physical activity, moderate physical activity, moderate to vigorous physical activity and vigorous physical activity (min/day), using previously applied and established cut points [20, 21]. All analyses were based on accumulation of data over 10 s epochs.

